#### Translational research

All patients will be asked for informed consent to collect blood samples for future translational research. An additional 20 ml blood is drawn during regular blood draws before start of the neoadjuvant chemotherapy, before chemoradiotherapy, before surgery, three months after surgery, and once a year during three years of follow-up, resulting in 7 samples. In addition, all patients will be asked for informed consent to collect fresh frozen tumour tissue obtained during surgery for translational research.

### Outcomes

The primary outcome of this study is the CR rate, defined as the presence of a pCR or a cCR. A pCR is defined as the absence of viable tumour cells at pathological examination of the resected specimen [22, 64]. A cCR is defined as the sustained absence of tumour tissue 1 year after treatment as assessed during clinical evaluations [16, 17]. Since the MEND-IT study is a phase II study, the CR rate observed in this trial will be compared to the CR rate as described in current literature for patients with hr-LARC treated with chemoradiotherapy alone (i.e. 10%) [32, 33]. In addition, the results of the MEND-IT trial will be compared to results of comparable cohorts treated with different treatment regimens.

Secondary objectives comprise the number of patients proceeding to surgery, the 3- and 5-year local recurrence-free, distant metastasis-free, progression-free, disease-free and overall survival. In addition, radiological response, pathological response, R0 resection rate, toxicity, treatment compliance rate, surgical morbidity, quality of life, and costs will be evaluated. Local recurrence-free survival is defined as the interval between surgery and a local recurrence. Metastasis-free survival is defined as the interval between inclusion and the detection of distant metastases. Progression-free survival will be calculated from inclusion onwards to the date of clinically or histopathologically proven distant metastases, a local recurrence, or the date of death from any cause, whichever occurs first. Disease-free survival will be calculated from the date of surgery onwards or the date of the second restaging MRI in case of a cCR until the date of a local recurrence, distant metastasis, or death from any cause, whichever occurs first. Overall survival will be calculated from the date of inclusion until the date of death from any cause. Toxicity from neoadjuvant treatment will be presented according to the NCI (US National Cancer Institute) Common Terminology Criteria for Adverse Events (CTCAE) v5.0 [65]. Perioperative complications will be presented according to the Clavien-Dindo grading system [66]. Pathological response will be presented according to the Mandard grading system [64].

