## Background

Locally advanced rectal cancer (LARC) is often defined as a clinically staged (c) T3 tumour within 1 mm from the mesorectal fascia (MRF), a cT4 tumour, cN2 disease, or rectal cancer in the presence of extramesorectal lymph nodes [1–3]. Standard treatment consists of neoadjuvant chemoradiotherapy prior to surgery, i.e. a total mesorectal excision [1, 4, 5]. However, despite optimal treatment, LARC is associated with local recurrence and distant metastasis rates ranging between 5–10% and 25–40%, respectively [5–12]. This has resulted in an ongoing search for better treatment regimens in patients at high risk of treatment failure.

The main aim of neoadjuvant treatment is to obtain downstaging to facilitate a resection with clear resection margins (R0) [5, 6, 13]. An R0 resection is an important prognostic factor for disease-free survival, particularly due to an improved local recurrence-free survival [5, 8, 14, 15]. In addition, the introduction of neoadjuvant treatment regimens has translated into new treatment strategies, focusing on organ preservation [16–19]. Previous studies reported a pathological complete response (pCR) rate, i.e. the absence of malignant cells on pathological examination after surgery, in over 15% of the patients treated with neoadjuvant chemoradiotherapy [16, 20–22]. Improved long-term outcomes, probably related to a favourable tumour biology, have been suggested in patients with a pCR [22, 23]. Subsequently, an organ preservation strategy with active surveillance, referred to as a watch and wait (W&W) strategy, has been introduced to prevent unnecessary surgical morbidity and mortality without comprising (disease-free) survival [16–19].

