
Hence, neoadjuvant chemotherapy in combination with (chemo)radiotherapy may improve short- and long-term outcomes in LARC. However, the absence of a substantial improvement in overall survival, the increased risk of treatment-related toxicity, possibly resulting in treatment delays, the differences in patient selection and treatment regimens among different studies, and the underrepresentation of patients with the prognostic most unfavourable rectal tumours hamper the clinical implementation of neoadjuvant chemotherapy in rectal cancer [29, 31, 36–40]. Moreover, overrepresentation of patients who do not need additional systemic treatment for cure, may also dilute positive oncological results. As a consequence, it has been hypothesised that total neoadjuvant treatment, consisting of both neoadjuvant chemotherapy and chemoradiotherapy, should be preserved for a select group of patients facing the worst prognosis [31].

Since the start of the RAPIDO trial in 2011, imaging-based staging has been further refined [33]. High-risk imaging-based features were more routinely described and studied, which resulted in the recognition of clinically important, unfavourable characteristics on MRI [33, 41–43]. An involved MRF, defined as a distance of ≤ 1 mm to the MRF, has already been recognized as an important, unfavourable prognostic feature for several years [44, 45]. In addition, the identification of EMVI, tumour deposits, or enlarged extramesorectal (lateral) lymph nodes (LLN) with a short-axis of at least 7 mm on baseline MRI has been suggested to identify patients with the most ‘ugly’ LARC, at high risk of failure on current treatment regimens [33, 42, 46–51]. A significantly decreased disease-free and overall survival rate has been described for patients with EMVI-positive rectal cancer, with 5-year distant metastasis rates up to 45.2%, compared to EMVI-negative rectal cancer (25.7%) [12]. In addition, the presence of tumour deposits on baseline MRI has been identified as an independent prognostic factor, indicating a poor survival [42, 52]. Lastly, a lateral local recurrence rate of up to 19.5% has been described in patients with lateral lymph nodes, located in the iliac or obturator compartment, with a short-axis of at least 7 mm on baseline MRI despite treatment with chemoradiotherapy prior to a total mesorectal excision [48].

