### Statistical methods

Demographics, patient, and tumour characteristics will be presented for all patients. Continuous data will be reported as mean with a standard deviation or as median with an interquartile range or 95% confidence interval, depending on the distribution. Categorical data will be reported as count, including a percentage. All statistical tests will be two-sided and a P-value of less than 0.05 will be considered as statistically significant.

The proportion of patients with a CR, defined as a pCR or a sustained cCR, will be compared to the CR rate of a comparable group of patients treated with chemoradiotherapy alone before surgery, as described in the available literature (i.e. 10%), performing a chi-squared goodness-of-fit-test.

The Kaplan–Meier method will be used to display survival curves. In addition, Hazard Ratio’s will be calculated using the Cox proportional hazard regression model and will be accompanied by 95% confidence intervals. Perioperative morbidity, surgical characteristics, and histopathological findings will be presented for all patients treated with a surgical resection. The incidence of toxicity related to neoadjuvant treatment will be presented separately for neoadjuvant chemotherapy and chemoradiotherapy. Health-related quality of life is graphically presented across all time points. Moreover, quality of life will be compared during those different time points using the ‘repeated measures ANOVA’. Incremental costs are calculated for the extra costs per additional patient alive and the extra costs per additional quality adjusted life year, respectively. The 95% confidence intervals for (differences in) costs and health outcomes will be generated by non-parametric bootstrapping, drawing samples of the same size as the original samples.

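### Metastasis-free and local recurrence-free survival leave out death, so Kaplan–Meier figures for them show neither event-free survival nor actual recurrence risk

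*Protocol article*

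**What the plan says.** The Outcomes section of the protocol article lists among the secondary objectives "the 3- and 5-year local recurrence-free, distant metastasis-free, progression-free, disease-free and overall survival". It then defines them one by one.

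- Local control: "Local recurrence-free survival is defined as the interval between surgery and a local recurrence".
- Distant control: "Metastasis-free survival is defined as the interval between inclusion and the detection of distant metastases".
- Progression-free survival runs from inclusion to "distant metastases, a local recurrence, or the date of death from any cause, whichever occurs first".
- Disease-free survival runs from surgery, or from the second restaging MRI after a clinical complete response, "until the date of a local recurrence, distant metastasis, or death from any cause, whichever occurs first".
- Overall survival ends at death from any cause.

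Death is therefore an event in three of the five endpoints and absent from the other two.

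Under Statistical methods the estimator is given in one sentence: "The Kaplan–Meier method will be used to display survival curves". Hazard ratios come from a Cox model. No cumulative incidence or competing-risk method is named, and no censoring rule for death is stated.

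**The concern.** The two definitions, their names and the only named estimator do not fit together. A name ending in -free survival tells the reader that the curve shows patients alive and free of the event. With death not an event, Kaplan–Meier removes a patient who dies first from the risk set as if the recurrence could still happen. The curve then shows neither the proportion alive and event-free nor, through its complement, the proportion who actually recur. It shows a net quantity for a setting without death, and even that requires death to be unrelated to recurrence. This is doubtful for local recurrence, because many deaths will follow distant metastasis.

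Absolute figures matter here. The trial has one arm, and Outcomes says its results will be set against comparable cohorts treated differently. No concurrent arm shares the same convention. The Background cites 5-year differences of 10% versus 7% for locoregional failure and 23% versus 31% for distant metastasis, so a shift of a few points, or a comparison with a cohort that counts death, could change the reading.

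**Working it through.** The article gives no planning figure for these two endpoints, so there is nothing to reproduce. The check asks how far the three possible quantities differ.

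**Inputs from the article.** Background: "LARC is associated with local recurrence and distant metastasis rates ranging between 5–10% and 25–40%, respectively". Also from Background, for disease with extramural venous invasion: "with 5-year distant metastasis rates up to 45.2" per cent.

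**Assumptions.** These rates are read as 5-year net risks *m* (1 − Kaplan–Meier with deaths censored). The article does not say how they were estimated and gives no time horizon for the ranges. The risk of death without the event, *d*, is on the same net scale and is not in the article. It is varied from 5% to 20% for metastasis and from 10% to 40% for local recurrence. The second range is wider because deaths after metastasis also precede local recurrence. Cause-specific hazards are taken as constant over 5 years.

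**Formulas.** With a = −ln(1 − m)/5 and b = −ln(1 − d)/5:

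- Kaplan–Meier with deaths censored: 1 − m
- True event-free survival (death an event): (1 − m)(1 − d)
- Cumulative incidence with death competing: a/(a + b) × [1 − (1 − m)(1 − d)]

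**Worked case.** m = 45.2%, d = 20%. Here 5a = 0.601 and 5b = 0.223, so a/(a + b) = 0.729. Event-free survival is 0.548 × 0.80 = 43.8%. Cumulative incidence is 0.729 × 0.562 = 41.0%.

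**Distant metastasis (%)**

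| m (= 1 − KM) | d | KM curve | True event-free | Gap | Cumulative incidence | 1 − KM too high by |
|---|---|---|---|---|---|---|
| 25.0 | 5 | 75.0 | 71.3 | 3.8 | 24.4 | 0.6 |
| 25.0 | 10 | 75.0 | 67.5 | 7.5 | 23.8 | 1.2 |
| 25.0 | 20 | 75.0 | 60.0 | 15.0 | 22.5 | 2.5 |
| 40.0 | 5 | 60.0 | 57.0 | 3.0 | 39.1 | 0.9 |
| 40.0 | 10 | 60.0 | 54.0 | 6.0 | 38.1 | 1.9 |
| 40.0 | 20 | 60.0 | 48.0 | 12.0 | 36.2 | 3.8 |
| 45.2 | 5 | 54.8 | 52.1 | 2.7 | 44.2 | 1.0 |
| 45.2 | 10 | 54.8 | 49.3 | 5.5 | 43.1 | 2.1 |
| 45.2 | 20 | 54.8 | 43.8 | 11.0 | 41.0 | 4.2 |

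**Local recurrence (%)**

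| m (= 1 − KM) | d | KM curve | True event-free | Gap | Cumulative incidence | 1 − KM too high by |
|---|---|---|---|---|---|---|
| 10.0 | 10 | 90.0 | 81.0 | 9.0 | 9.5 | 0.5 |
| 10.0 | 20 | 90.0 | 72.0 | 18.0 | 9.0 | 1.0 |
| 10.0 | 30 | 90.0 | 63.0 | 27.0 | 8.4 | 1.6 |
| 10.0 | 40 | 90.0 | 54.0 | 36.0 | 7.9 | 2.1 |

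At the lower local recurrence rate of 5%, 1 − KM is too high by about 0.3 points (d = 10%) to 1.1 points (d = 40%).

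The direction does not depend on constant hazards: whenever there are deaths without the event, censoring them raises both the curve and its complement above the quantities a reader would take them for. Only the sizes depend on the assumptions.

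**The case against.** The article is condensed and no analysis plan is shown. Its Kaplan–Meier sentence speaks only of displaying curves, and rules for censoring and competing events are commonly left to the analysis plan. It stands that censoring at death is implied rather than written. But the event definitions and the estimator are fixed in the article, and under them a patient who dies event-free can only be censored.

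The error in recurrence risk is also small against the trial's precision. With 128 patients, a binomial 95% half-width is 1.96 × √(0.10 × 0.90/128) = 5.2 points at 10%, and 1.96 × √(0.45 × 0.55/128) = 8.6 points at 45%. That stands as a limit on importance, although the error always goes one way and does not average out.

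Several stronger readings are tempting, and the article does not support them:

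- A reader might infer that every survival curve censors deaths. Progression-free, disease-free and overall survival count them, so deaths are not hidden from the efficacy results.
- A reader might infer a large overstatement of local recurrence, for example 20% against an actual 15.8% when 40% die first. The article gives 5–10% for locally advanced disease. Its nearest figure, up to 19.5%, is lateral recurrence in patients with enlarged lateral nodes. It gives no risk of death before local recurrence.
- A reader might take the gap of 9 to 36 points as estimation bias. It compares two estimands, recurrence alone and recurrence or death, so it measures how far the label misleads.
- A reader might infer that the Cox hazard ratios are invalid. With deaths censored they are legitimate cause-specific hazard ratios. The problem lies in the absolute 3- and 5-year figures.

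**Conclusion.** The point holds for two secondary endpoints. As defined, and with Kaplan–Meier the only named estimator, their 3- and 5-year figures would overstate the share alive and event-free, and their complement would overstate the risk of recurrence.

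Against cumulative incidence the overstatement is modest: about 0.6 to 4 points for metastasis (net risk 25–45.2%, death without metastasis 5–20%) and about 0.5 to 2 points for local recurrence (net risk 10%, death without it 10–40%). Against true event-free survival the curve is about 3 to 15 and 9 to 36 points too high, respectively. Every death rate is an assumption, the article's rates are read as 5-year net risks, and 3-year figures were not computed.

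The primary complete response endpoint and the sample size of 121 (128 with drop-out) do not use these definitions and are unaffected.

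**What to change.** Choose one of two consistent forms for both endpoints:

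1. Rename them local recurrence and distant metastasis, and report 3- and 5-year cumulative incidence by the Aalen–Johansen estimator with death without the event as the competing event. The planned Cox model with deaths censored can stay, labelled as giving cause-specific hazard ratios.
2. Keep the -free survival names, add death from any cause as an event to both definitions, and keep Kaplan–Meier.

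The first form answers the question of local and distant control directly. The second gives composites in line with progression-free and disease-free survival. Whichever is chosen, comparisons with other cohorts should use figures defined in the same way.

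The cost is a small amendment to two secondary definitions, and the sponsor would have to judge whether it counts as substantial under the Protocol amendments section. No new data are needed, because dates of death are already required for overall, progression-free and disease-free survival.

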#### Neoadjuvant chemotherapy

All included patients will receive neoadjuvant (induction) chemotherapy within 4 weeks after inclusion. Neoadjuvant chemotherapy consists of six two-weekly cycles of FOLFOXIRI (irinotecan 165 mg/m^2^ Body Surface Area (BSA), oxaliplatin 85/m^2^ BSA, leucovorin 400 mg/m^2^ BSA, 5-flourouracil 3200 mg/m^2^ BSA). Dose reductions are permitted on discretion of the medical oncologist.

Restaging will be performed with a pelvic MRI and a thoraco-abdominal computed tomography (CT) scan after four cycles of FOLFOXIRI. The timing of restaging should not interfere with the potential continuation of neoadjuvant chemotherapy. Radiological evaluation will be performed by a radiologist with expertise in abdominal imaging conform a standard operating procedure. The results will be discussed during a MDT meeting in one of the participating centres in the attendance of at least a surgical oncologist, a medical oncologist, a radiation oncologist, and a radiologist with expertise in abdominal imaging. If a patient has stable or responsive disease, neoadjuvant chemotherapy will be continued with two additional cycles of FOLFOXIRI. Subsequently, chemoradiotherapy will start within 3–6 weeks after the last cycle of neoadjuvant chemotherapy. If progressive, but still resectable disease is assumed during restaging, no further systemic therapy will be administered, and the patient will start with chemoradiotherapy within 3–6 weeks. If restaging suggests progressive, unresectable disease or the presence of distant metastases, the best palliative treatment will be offered according to standard of care.

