#### Treatment evaluation

Six to eight weeks after the last day of the chemoradiotherapy, restaging will be performed with a pelvic MRI and a thoraco-abdominal CT scan. The results will be discussed during a MDT meeting. A surgical resection will be planned for all patients with resectable disease after neoadjuvant treatment. In case of a cCR, a W&W strategy with close surveillance may be discussed with the patient by the treating physician according to standard of care. The presence of distant metastases or unresectable local disease will result in the best palliative treatment according to standard of care.

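### Progression-free survival starts at inclusion but leaves out local progression before resection, so a tumour that becomes unresectable without metastasis is not an event

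*Protocol article*

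**What the plan says.** All endpoint definitions are in the protocol article under Outcomes.

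- PFS is one of several secondary endpoints, reported as part of "the 3- and 5-year local recurrence-free, distant metastasis-free, progression-free, disease-free and overall survival".
- Its start: "Progression-free survival will be calculated from inclusion onwards".
- Its end: "to the date of clinically or histopathologically proven distant metastases, a local recurrence, or the date of death from any cause", whichever comes first. The list is closed.
- For local recurrence: "Local recurrence-free survival is defined as the interval between surgery and a local recurrence".
- Disease-free survival (DFS) has the same three events as PFS. It starts at surgery, or at the second restaging MRI for a patient with a clinical complete response.
- Metastasis-free and overall survival both start at inclusion. Neither counts local progression.

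The treatment sections foresee local failure before resection.

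- Neoadjuvant chemotherapy, restaging after four cycles: "If restaging suggests progressive, unresectable disease or the presence of distant metastases, the best palliative treatment will be offered".
- The same section describes a milder course: "If progressive, but still resectable disease is assumed during restaging, no further systemic therapy will be administered". These patients go on to chemoradiotherapy.
- Treatment evaluation, restaging after chemoradiotherapy: "The presence of distant metastases or unresectable local disease will result in the best palliative treatment".

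**The concern.** An endpoint named progression-free survival that starts before treatment should register progression of the tumour under treatment. This one registers metastasis but not local growth. Two patients can leave the curative pathway at the same restaging, one with metastases and one with a locally unresectable tumour. The first has a PFS event that day. The second has none until metastasis or death.

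What is at stake is the meaning of the reported 3- and 5-year PFS. Outcomes also says that results will be compared with those of cohorts given other regimens. A PFS that ignores local progression cannot be read against one that counts it.

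**Working it through.** **1. The plan's own figure.** No figure is stated for PFS. The only design calculation is for the CR rate (Sample size): 10% against 20%, 5% significance, 90% power, with two-sided tests (Statistical methods).

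n = [(1.960·√(0.1·0.9) + 1.282·√(0.2·0.8)) / 0.1]² = 121.13, against 121 stated. With 5% drop-out, 121/0.95 = 127.4, so 128 as stated. PFS does not enter, so nothing below touches the sample size or the primary test.

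**2. Does any time-to-event endpoint date the failure?** Take a patient found locally unresectable at a restaging, without metastasis, never resected and without a clinical complete response.

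| Endpoint | Start | Local progression counted? |
|---|---|---|
| PFS | Inclusion | No; event only at metastasis or death |
| Metastasis-free survival | Inclusion | No |
| Overall survival | Inclusion | No |
| DFS | Surgery, or second MRI if complete response | Clock never starts |
| Local recurrence-free survival | Surgery | Clock never starts |

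None does. PFS has the events of DFS with an earlier start. The interval it adds, from inclusion to surgery, is the one in which local progression of the primary tumour can occur.

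**3. Direction.** Adding an event type leaves each patient's PFS time the same or makes it shorter. The underlying PFS as written is therefore never lower than PFS with local progression counted.

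**4. Size, as an illustration.** The documents give no rate of isolated local unresectability, so these inputs are assumptions:

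- share affected f = 4-10%, which is 128 × 0.04 = 5.1 to 128 × 0.10 = 12.8 patients;
- local failure at month 6;
- exponential time from then to metastasis or death, with median m = 12 or 18 months.

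Once local failure is counted, the affected patients contribute nothing to PFS after month 6. The overstatement at month t is therefore

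Δ(t) = f · exp(−ln 2 · (t − 6)/m) = f · 2^(−(t − 6)/m).

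| t | m | Fraction still event-free as written | Δ for f = 4% | Δ for f = 10% |
|---|---|---|---|---|
| 36 months | 12 | 2^(−2.5) = 0.177 | 0.7 points | 1.8 points |
| 36 months | 18 | 2^(−1.667) = 0.315 | 1.3 points | 3.1 points |
| 60 months | 12 | 2^(−4.5) = 0.044 | 0.2 points | 0.4 points |
| 60 months | 18 | 2^(−3) = 0.125 | 0.5 points | 1.3 points |

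A second set of assumptions (2-10% affected at month 3, median 1 to 2 years) gives 0.3 to 3.9 points at 3 years, which is the same order.

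**5. Scale.** If 3-year PFS were near 60% (assumed), the 95% interval with 128 patients would be about ±1.96·√(0.6·0.4/128) = ±8.5 points. The overstatement lies within sampling error, but it is systematic and in one direction.

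**The case against.** **Local recurrence may have been meant loosely.** DFS applies the term to unresected patients with a clinical complete response, so it does not strictly require an operation. That is true, but the term still presupposes a tumour that was removed or had cleared. The treatment sections use a different word for growth under treatment. The gap stays open.

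**The failure is visible elsewhere.** The number of patients going on to surgery and radiological response are secondary outcomes, and a patient with unresectable disease cannot be a complete responder. This stands and limits the harm. None of these dates the failure, however, so they do not repair PFS.

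**The size is uncertain and small.** This stands. The nearest figure is in the Discussion: 92% of the experimental arm in the cited phase III trial of triplet chemotherapy reached surgery. That leaves 8% who did not, for all reasons together, in a population the protocol regards as less unfavourable. It neither confirms nor caps the assumed 4-10%.

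A reader might also infer stronger claims that the document does not support.

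- That PFS is the only disease-control endpoint starting at inclusion. Metastasis-free survival starts there too; PFS is the only composite disease-control endpoint that does.
- That the omitted event is the most typical failure in these patients. The Discussion stresses their particular risk of metastasis, which PFS counts. The Background gives 25-40% metastasis against 5-10% local recurrence in locally advanced disease. Eligibility requires disease deemed resectable.
- That PFS is inflated by 3 to 8 points. The formula gives that at 12 months with an 18-month median (2^(−1/3) = 0.794, so 3.2 to 7.9 points), but 12 months is not a planned PFS time point.
- That affected patients are lost to follow-up and cause informative censoring. Nothing says that they leave follow-up.

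**Conclusion.** The point holds as an error in a stated secondary endpoint definition. It is not a detail left to an analysis plan, because the event list is explicit and closed. A patient who becomes locally unresectable before resection, without metastasis, is counted as progression-free until metastasis or death, and no time-to-event endpoint dates that failure.

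The direction is certain: PFS can only look better than it should. The size rests on the assumed share, timing and median shown above. On those it is about 0.7-3 points at 3 years and at most about 1.3 points at 5 years. These figures cover unresectable disease only; counting progression that leaves the tumour resectable would widen the difference by an amount the documents cannot show.

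A reader might infer that the trial's main conclusion is at risk. It is not: no sample size or hypothesis test is stated for PFS, and the CR comparison and the 121/128 patients stand as they are.

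**What to change.** In the PFS definition under Outcomes:

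- Add local progression as an event, at minimum disease that becomes or is found unresectable at restaging or at operation.
- Date it at the imaging or operation that shows it.
- State explicitly whether local progression that leaves the tumour resectable is an event. The Neoadjuvant chemotherapy section treats this as a separate course, with the patient continuing to chemoradiotherapy, so a bare reference to local progression would leave it ambiguous.

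The cost is a line or two of text and a slightly less favourable secondary PFS. The restaging MRI scans and their multidisciplinary review are already scheduled, so no further assessment is needed. The change concerns the endpoint definition only and alters nothing in clinical management.
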